## Background

Bipolar Disorder (BD) is a severe, complex genetic disorder with a wide range of clinical presentations and a multifactorial etiology (Grande et al. 2016). It ranks as the 6th highest disease burden worldwide and contributes significantly to the global economic burden. BD is a critical public health concern due to its high prevalence (more than 1% of the world's population), chronic nature, high disability rate, and association with both psychiatric and Medical Comorbidities (MC) (Grande et al. 2016). Patients with BD have an elevated risk of cardiovascular disease (CVD) mortality, resulting in a reduced life expectancy of 10–20 years (Miller and Bauer 2014; Laursen 2011; Roshanaei-Moghaddam and Katon 2009), primarily due to a high level of MC in this population (Roshanaei-Moghaddam and Katon 2009), such as type 2 diabetes, CVD, musculoskeletal disorders, renal disorders, neurological disorders, and metabolic syndrome (MetS) (McIntyre et al. 2007). The heightened cardiovascular mortality in individuals with BD is possibly due to multiple factors. Medications like lithium and valproic acid may lead to weight gain and disrupt glucose metabolism, while second-generation antipsychotics are linked to hyperlipidaemia, insulin resistance, and weight gain (Weiner et al. 2011), nonetheless, despite these associations, long-term treatment with antipsychotic drugs has been correlated with lower mortality rates when compared to individuals who do not use antipsychotics (Tiihonen et al. 2009). Lifestyle factors such as poor diet, inadequate exercise, and higher rates of smoking further compound these risks. As a result, common cardiovascular risk factors like obesity, hypertension, diabetes, and hyperlipidemia are more prevalent among those with BD, amplifying their susceptibility to cardiovascular mortality (Weiner et al. 2011; Swartz and Fagiolini 2012). In addition, MC in BD are associated with unfavourable medical outcomes of this mental disorder such as treatment resistance, mood relapse or cognitive disorders (Bauer et al. 2018). Factors contributing to these higher MC rates in BD include pathogenic links between a variety of risk factors such as pathogenic and biological factors (e.g., metabolic, or immune system disorders, genetic susceptibility), medication exposure, unhealthy lifestyles, underutilization of health services, and co-occurring mental disorders (Keck and McElroy 2003; Carney and Jones 2006; Chengappa et al. 2000; Liese et al. 1998). Furthermore, the interplay of genetic susceptibility and underlying physiological processes, including heightened activation of immunometabolic or endocrine systems in both central and peripheral contexts, contributes to the development of both MetS and psychiatric disorders (Penninx and Lange 2018). MetS is a complex and multifaceted medical condition characterized by a cluster of interconnected risk factors that significantly increase the risk of heart disease, stroke, and type 2 diabetes. These risk factors often occur together and share common underlying mechanisms (Eckel et al. 2005). While there is no single universally accepted definition of MetS, several major health organizations and expert groups have agreed on three out of the five criteria listed in Table 1 required to fulfill a diagnosis of MetS (Alberti et al. 2009). The MetS is significantly more prevalent (by 1.98 times) in patients with BD than in the general population (Vancampfort et al. 2013; Godin et al. 2024; Godin et al. 2014). This high prevalence rate is plausibly explained by a range of multiple factors, including medication side effects, unhealthy lifestyles, and pathogenic and biological factors (Firth et al. 2020). For example, certain antipsychotic medications are associated with weight gain and insulin resistance, which in turn increase the risk of developing MetS. In addition, people with BD experience periodic mood fluctuations that affect their ability to maintain a healthy lifestyle (Penninx and Lange 2018). Physical activity (PA) and sleep patterns play important roles in MetS development. MetS is positively associated with physical inactivity and sedentary behaviour, while healthy sleep patterns benefit cardiometabolic health (Amirfaiz and Shahril 2019; Huang and Redline 2019). It is proven that patients with BD are typically less active, more sedentary, and experience poorer sleep quality (Janney et al. 2014; Brochard et al. 2018). Despite the high MC prevalence in BD, patients often receive inadequate diagnoses and treatment, and comprehensive studies on this topic remain limited, hindering personalized plans and preventive treatments. Neglecting comorbidities in BD management creates relevant obstacles to early and effective interventions for patients. For all these reasons, collaborative efforts between mental health and medical services are essential to enhance diagnosis and treatment, improve quality of life, and reduce comorbidity-related mortality in patients with BD.

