### Study design

#### Study 1: the registry study

The consortium, drawing on extensive genetic epidemiology expertise, will leverage Swedish and Norwegian national registers and biobanks with (single-nucleotide polymorphism) SNP-array genotyped samples. It will begin by identifying adult Swedish residents from the Swedish National Patient Register and the Swedish Prescribed Drug Register, with registered treatment contact for BD. A similar process will be implemented with Norwegian registers. Subsequently, the consortium will investigate diagnosed MC, comparing individuals with and without BD. The primary focus of the Swedish and Norwegian teams is to explore the associations between BD onset and MC risk, with a specific emphasis on MetS. Additionally, it will include type 2 diabetes and CVD as relevant outcome variables due to their strong association with MetS. Research outcomes will be determined using a combination of diagnostic data from patient registers and pharmacological treatment details from the prescribed drug register, as shown in Table 2. Furthermore, risk prediction models for cardiometabolic conditions in individuals with BD will be developed, with CVD and type 2 diabetes as primary outcomes, and MetS, and all-cause and cause-specific mortality, as secondary outcomes. Given the absence of complete MetS diagnostic criteria in Swedish population registries, the consortium will use several related medical conditions as proxies (e.g., obesity, hypertension, hyper/dyslipidaemia). Access to genotyping data from approximately 1.3 million participants, derived from Illumina arrays or similar platforms in existing genotyped cohorts, will further enrich the study.

**Table 2 Tab2:** Socio-demographic and clinical characteristics to be used for the training set with the Swedish registry

1	Sex
2	Ethnicity
3	Age
4	Marital status
5	Children (yes/no)
6	Education years, Mean (SD)
7	Area of residence (urban/rural)
8	Current occupational status
9	Poverty (poor housing, malnutrition, etc.)
10	Age of first contact with mental health services (Years), Mean (SD)
11	Bipolar disorder I or II
12	Comorbidity with other mental disorders
13	Number of lifetime psychiatric hospitalizations
14	The overall length of psychiatric hospitalizations (months)
15	Lifetime substance or alcohol use disorder (yes/no)
16	Ever treated with lithium or mood stabilizers
17	Ever treated with antipsychotics
18	Number of diagnoses of MC lifetime

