#### Study 1: the registry study

For prediction modelling studies in Sweden, we will employ multivariate Cox proportional hazards regression analysis to develop 1-, 2- and 5-year risk prediction models separately for: CVD, and type 2 diabetes, as primary outcomes, as well as for proxy measures of MetS—hypertension, obesity and hyper/dyslipidaemia, and all-cause and cause-specific mortality as secondary outcomes, in individuals with BD. This will be done by combining traditional risk factors of cardiometabolic disorders (i.e., age, sex, a diagnosis/medication prescription for hypertension, diabetes mellitus (type 1 and type 2), hyperlipidaemia, obesity, and smoking; and family history), with potentially relevant novel predictors associated with both BD and an increased risk of cardiometabolic conditions (i.e., psychiatric comorbidity, use of psychotropic medication, and socio-demographic factors). We will use a limited backward stepwise procedure to determine whether to retain novel candidate predictors based on their p-values. Traditional risk factors will be kept in the model. With this approach we aim to retain predictors considered as traditional cardiometabolic risk factors based on clinical practice and previous studies, and to consider potentially relevant novel risk factors, with the final model being easily applicable by clinician, with satisfactory face validity. A bootstrapping method will be used for internal validation of the models with 200 bootstrap samples. To assess the discrimination of the models, the ROC curve and C-index will be used. To assess the calibration of the models we will use the Integrated Brier Score and calibration plots. We will also compare the performance of the models that includes only traditional risk factors with the models that include additional novel risk factors by calculating the Net Reclassification Index (NRI) and the Integrated Discrimination Improvement (IDI) index. We will also test the performance of the models across the following subgroups: males/females, and aged younger than 50/50 and older. Machine Learning (ML) algorithms for survival analysis will be tested on Swedish and Norwegian register data, considering a large number of available potential risk indicators such as demographics, electronic medical records, and genotypes. The overarching research question is to explore if ML algorithms based on many predictors may improve the predictive accuracy. For the ML algorithms, the data will be split into a 60% training set, 20% validation set, and 20% test set. Four models will be trained: penalized Cox regression, random survival forest, gradient boosting machine, and survival support vector machine. Hyperparameters will be tuned on the validation set. Model discrimination will be evaluated with C-index and cumulative/dynamic AUC. Calibration will be assessed with the Integrated Brier Score. Performance metrics on the test set will determine the final model. Sensitivity analyses will explore model accuracy when considering predictors related to patient history and dispensed medications only. We will also assess model performance separately in Sweden and Norway. Furthermore, we will merge register data from Norway and Sweden with biobank data (N ~ 1.3 million) to evaluate whether adding genotypes improves predictive power.

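### The registry risk models plan separate Cox regressions for absolute risk with no step for death as a competing event, which can overstate mainly the 5-year risks in older patients

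*Protocol article*

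**What the plan says.** In the protocol article, Data analyses, Study 1: the registry study, the method is "multivariate Cox proportional hazards regression analysis to develop 1-, 2- and 5-year risk prediction models". The models are fitted separately for CVD and type 2 diabetes as primary outcomes. Secondary outcomes are hypertension, obesity and hyper/dyslipidaemia as proxies for MetS, and "all-cause and cause-specific mortality as secondary outcomes, in individuals with BD".

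On performance, the section says: "To assess the calibration of the models we will use the Integrated Brier Score and calibration plots". Discrimination is assessed by ROC curve and C-index, and performance is to be tested in the subgroups "males/females, and aged younger than 50/50 and older". The machine-learning arm names "penalized Cox regression, random survival forest, gradient boosting machine, and survival support vector machine", assessed by C-index, cumulative/dynamic AUC and Integrated Brier Score.

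The cohort starts from "identifying adult Swedish residents from the Swedish National Patient Register and the Swedish Prescribed Drug Register" (Study design, Study 1), with no upper age limit stated. The Background describes raised cardiovascular mortality in bipolar disorder, "resulting in a reduced life expectancy of 10–20 years".

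The article does not mention competing events, cumulative incidence or a subdistribution model. Nor does it mention combining the disease models with a model for death.

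**The concern.** The product of these models is an absolute risk at a fixed horizon, not only a hazard ratio. A patient who dies without diabetes can no longer develop it. A Cox model for diabetes alone censors that patient at death, and 1-S(t) is then the risk in a hypothetical population where nobody dies first. It is higher than the real-world risk whenever any deaths occur.

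Which deaths compete depends on the outcome:

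- **Type 2 diabetes and the MetS proxies:** any death before the diagnosis.
- **CVD:** only deaths that are neither counted as a CVD event nor preceded by one.
- **Cause-specific mortality:** deaths from all other causes, by definition.
- **All-cause mortality:** nothing competes.

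The planned checks might not show the problem. The C-index measures ranking, not the level of risk. Calibration plots against Kaplan-Meier estimates, and a Brier score that also censors deaths, would share the bias and could look satisfactory.

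**Working it through.** **The plan's own figure.** The only numerical result in the sample-size section for these models is the minimum of 4,199 patients. With 24 predictors, shrinkage 0.90 and R² 0.05, n = 24 / [(0.90 - 1) × ln(1 - 0.05/0.90)] = 4,198.86, rounded up to 4,199. It reproduces, and it has no bearing on this point.

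**Inputs for the check.** The horizons of 1, 2 and 5 years come from the article. The outcome hazard h1 and the hazard of death without the outcome h2 are assumptions, taken as constant and shown over a range.

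**Formulas.**

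- Risk with deaths censored: 1 - exp(-h1·t)
- Cumulative incidence: h1/(h1+h2) × [1 - exp(-(h1+h2)·t)]
- Relative excess: the first divided by the second, minus 1. For small rates it is roughly h2·t/2.

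**One case in full.** Take h1 = 0.02, h2 = 0.03, t = 5. With deaths censored, 1 - exp(-0.10) = 9.52%. The cumulative incidence is 0.02/0.05 × [1 - exp(-0.25)] = 0.4 × 0.2212 = 8.85%. The relative excess is 9.52/8.85 - 1 = 7.6%. The approximation gives 0.03 × 5/2 = 7.5%.

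**Range, with h1 = 2% per year.**

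| Competing death rate per year | Excess at 1 year | Excess at 2 years | Excess at 5 years | 5-year risk, deaths censored v cumulative incidence |
|---|---|---|---|---|
| 0.5% | 0.2% | 0.5% | 1.2% | 9.52% v 9.40% |
| 1% | 0.5% | 1.0% | 2.5% | 9.52% v 9.29% |
| 3% | 1.5% | 3.0% | 7.6% | 9.52% v 8.85% |
| 6% | 3.0% | 6.1% | 15.5% | 9.52% v 8.24% |
| 10% | 5.1% | 10.3% | 26.5% | 9.52% v 7.52% |

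The largest 2-year entry, 10.3%, is 3.92% against 3.56%, a difference of 0.36 percentage points.

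**Sensitivity to the outcome rate.** Varying h1 from 0.5% to 4% per year moves the 5-year excess only between 7.4% and 7.7% at a death rate of 3%, and between 15.2% and 15.7% at 6%. The article's expected 12,000 events in 40,000 patients over an average of 2 years gives a crude h1 of 12,000/(40,000 × 2) = 0.15 per year. With that rate the 5-year excess is 1.1% at a death rate of 0.5%, 2.2% at 1%, 6.7% at 3%, 13.6% at 6% and 23.3% at 10%. The pattern is the same.

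**The case against.** The strongest reply is that an error is being inferred from silence. The article does not say that deaths are censored, nor how risks are computed from the hazards. Cox models are a legitimate ingredient of a competing-risk analysis, and models for both disease and death are already planned in the same data. A condensed article may leave the combining step to a fuller document. This stands in part: the point is conditional on the default handling of deaths. But the article fixes both the model and the target, an absolute risk, and goes down to the number of bootstrap samples and the reclassification indices. Followed as written, the plan does not yield real-world risk. The planned all-cause mortality model would not by itself fill the gap, because it also counts deaths after the outcome.

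Three stronger readings are tempting and not supported:

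- **That risks at all three horizons are materially too high.** The table shows an excess of at most 3% at 1 and 2 years unless competing mortality is well above 3% per year.
- **That risks in the 50-and-over subgroup are 15-26% too high.** This needs competing death rates of about 6-10% per year. The article gives no death rates and no age distribution, and a shortened life expectancy is not an annual rate. At a constant 10% per year the mean remaining life is 1/0.10 = 10 years, which nothing in the article shows for everyone aged 50 or over. For CVD, total mortality also overstates the competing rate.
- **That the low, medium and high categories of the Clinical Support Tool are biased.** The Discussion gives no cut-offs and does not say that the Cox risks set the categories. The first planned validation uses baseline data from the clinical study, whose participants are aged 18-65.

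The article plans to test performance by age group but does not name calibration there, so a biased subgroup calibration cannot be asserted either.

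**Conclusion.** The point holds in a limited form. Separate Cox models without a competing-risk step overstate absolute risk if deaths are censored and risk is read as 1-S(t). The direction is certain under that condition. The size depends on death rates that the article does not give.

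On the assumed constant hazards, the excess is negligible for younger patients at every horizon and generally small at 1 and 2 years. At 5 years it reaches about 7.5% in relative terms at a competing death rate of 3% per year, and more only at higher rates. It therefore matters mainly for the 5-year models in older patients. Hazard ratios remain valid as cause-specific effects, and the all-cause mortality model is unaffected. No effect on the Clinical Support Tool's category limits can be shown. It is worth correcting before the models are fitted, because the better method is standard.

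**What to change.** For every outcome except all-cause mortality, state which deaths compete and derive the 1-, 2- and 5-year risks from the cumulative incidence. Either of two routes serves:

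- Fit a cause-specific Cox model for the outcome and another for competing death, the latter with follow-up ending at the outcome, and combine them.
- Fit a Fine-Gray model.

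For CVD, say whether fatal CVD counts as an event. Compute the calibration plots, Brier score and time-dependent AUC on the same competing-risk basis, and report them for patients under 50 and from 50 years. State the same for the machine-learning models wherever they are used to give absolute risks.

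The cost is some added wording and a little more analysis with standard software. No new data are needed, because all-cause and cause-specific mortality are already registry outcomes. Predicted risks will come out slightly lower.

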19	Number of lifetime hospitalizations in any medical wards
20	Body Mass Index (BMI)
21	Information about all drug prescriptions in the lifetime
22	Smoking (yes/no)
23	Sleep problems
24	Familiarity with diabetes and/or CVD

While leveraging national registers offers significant advantages, several limitations will have to be considered when interpreting findings from this study. First, the reliance on proxy conditions to represent MetS may introduce potential misclassification bias. The absence of complete diagnostic data in the registries limits the study's ability to accurately capture the true prevalence of MetS among individuals with BD. Additionally, individual proxies might not fully capture the complex interplay of factors contributing to MetS, potentially underestimating the true association between MetS and these outcomes in BD. Second, the study is inherently limited to information available in the registers, which may lack granularity around certain lifestyle factors, clinical metrics, and disease progression markers over time. Lastly, the utilization of specific-cause mortality outcomes should also be interpreted with caution due to potential discrepancies between recorded and actual causes of death (Brooke et al. 2017).

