### Power and sample size

#### Study 1: the registry study

To determine the required sample size for fitting a Cox proportional hazards model, recent guidelines were followed (Riley et al. 2019). With an estimated cohort of 40,000 incident patients with BD and an expected 12,000 outcome events based on a 31% prevalence rate (Engin 2017) the minimum required sample size was estimated to be 4,199 individuals for a model with 24 candidate predictors. This assumed an average 2-year follow-up, a shrinking factor of 0.90, and an anticipated R2 of 0.05. For the ML models, sample size calculations based on statistical power are not directly applicable, since these techniques focus on optimizing predictive performance (i.e., reducing a loss function) rather than hypothesis testing. Instead, sample size and model complexity will be considered when training (e.g., learning curves plots by sample size and several parameters).

With a large cohort of 40,000 patients, our study is adequately powered to develop and validate robust predictive models for MetS in patients with BD using both standard survival analysis and ML techniques. This will allow the identification of modest predictive effects across a range of candidate variables and the construction of accurate predictive models for MetS incidence in this population (Engin 2017; Peduzzi et al. 1995).

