#### Study 3: the exploratory clinical study

We estimated the sample size based on planned comparisons for 15 variables of interest (Table 6) for a two independent groups design (MetS + vs MetS−) assuming an expected proportion of Mets (at least three criteria out of five) of approximately 31%. With the estimated cohort of 400 subjects (180 Mets + , 220 Mets−), assuming a power of at least 80% and a significance level of 0.002 (to account for test multiplicity), we are going to be able to identify, at baseline, a significant effect size (ES) of 0.4 for independent t-tests (continuous variables) or an ES of 0.395 for a comparison of two independent proportions (assuming normal asymptotic test).

**Table 6 Tab6:** List of variables to be used for power calculation in the ECS at baseline

Sex	1. Female, male
Age	1. 18–45 years, 46–65 years
Marital status	1. Married, unmarried
Children (yes/no)	1. Yes, 2. No
Education years, mean (SD)	1. 0–10, > 10
Current occupational status	1. Employed, 2. Unemployed
Age of first contact with mental health services (Years), Mean (SD)	Continuous variable
Bipolar disorder I or II or NOS	1. Yes, 2. No
Comorbidity with other mental disorders	1. Yes, 2. No
Lifetime substance or alcohol use disorder	1. Yes, 2. No
Ever treated with lithium or mood stabilizers	1. Yes, 2. No
Ever treated with antipsychotics	1. Yes, 2. No
Number of diagnoses of MC lifetime assessed with Elixhauser	Continuous variable range 0–32
Body mass index	Continuous variable
Family history of diabetes and/or CVD	1. Yes, 2. No

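### The registry study claims power for MetS-incidence models, but no outcome listed for its Cox models is MetS as the protocol defines it

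*Protocol article*

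**What the plan says.** The Study design section for Study 1 announces registry prediction models "with CVD and type 2 diabetes as primary outcomes, and MetS, and all-cause and cause-specific mortality, as secondary outcomes". It then explains a substitution: "Given the absence of complete MetS diagnostic criteria in Swedish population registries, the consortium will use several related medical conditions as proxies".

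The Data analyses section for Study 1 says the Cox regressions are used "to develop 1-, 2- and 5-year risk prediction models separately for: CVD, and type 2 diabetes, as primary outcomes", and continues "as well as for proxy measures of MetS—hypertension, obesity and hyper/dyslipidaemia, and all-cause and cause-specific mortality as secondary outcomes". It gives no counting or co-occurrence rule.

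The limitations paragraph under Study design concedes that "the reliance on proxy conditions to represent MetS may introduce potential misclassification bias" and that "individual proxies might not fully capture the complex interplay of factors contributing to MetS".

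The Power and sample size section for Study 1 expects 12,000 events in 40,000 patients from a prevalence of 31%. It concludes that the cohort is large enough for robust MetS prediction, including "the construction of accurate predictive models for MetS incidence in this population". The matching section for Study 3 uses the same percentage, "assuming an expected proportion of Mets (at least three criteria out of five) of approximately 31" per cent. The Background (with Table 1) and the Study 3 analysis section also define MetS by three of the five criteria.

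**The concern.** MetS is defined by criteria occurring together. A model for hypertension, obesity or dyslipidaemia alone estimates the risk of something else, with its own event rate and its own leading predictors. The power section nevertheless speaks of MetS incidence as if no substitution had been made.

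Two things are at stake. Readers may take component models for MetS models, although MetS is the project's pilot condition. And the expected number of events is tied to the syndrome, so it says little about the event counts for the outcomes that will be fitted. The protocol also plans to check the Clinical Support Tool (CST) on MetS prediction in the clinical study, where MetS means three of five, without saying how the registry component models relate to that target.

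**Working it through.** **1. The plan's own figure.** The minimum sample size follows the shrinkage criterion n = p / [(S − 1) × ln(1 − R²/S)]. The registry power section gives p = 24 predictors, S = 0.90 and R² = 0.05.

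- ln(1 − 0.05/0.90) = −0.05716
- n = 24 / (0.10 × 0.05716) = 4,198.9, rounded up to 4,199

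This matches the protocol. The formula contains only p, S and R², so with those inputs the minimum does not depend on which outcome is modelled.

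**2. The event count.** 0.31 × 40,000 = 12,400. The stated 12,000 is 30% of 40,000, so it is probably rounded. The registry section does not say what the 31% is a prevalence of. The same figure is defined in the Study 3 power section as at least three of five criteria, and the registry section goes on to discuss MetS models. The natural reading is that the 12,000 are MetS cases.

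**3. The sections side by side.**

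| Section | MetS-related registry outcome |
|---|---|
| Study design, Study 1 | MetS, followed by a statement that proxies will be used |
| Data analyses, Study 1 (Cox models) | Three single conditions, modelled separately |
| Data analyses, Study 1 (machine learning) | Outcome not stated |
| Power and sample size, Study 1 | MetS incidence, events from 31% |
| Background; Data analyses, Study 3 | MetS is three of five criteria |

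The second and fourth rows do not describe the same outcome.

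**4. How far a single criterion is from MetS (illustration only).** Assumptions: five equally common criteria, a latent-normal model with equal pairwise correlation r, P(at least three of five) = 0.31, and perfect recording.

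For r = 0 this is binomial. Solving P(X ≥ 3) = 0.31 with X ~ Bin(5, q) gives q = 0.396. Given one particular criterion, MetS needs at least two of the other four: P(Bin(4, 0.396) ≥ 2) = 0.517. So 1 − 0.517 = 48% of people with that criterion do not have MetS. At r = 0.4, q = 0.354, the conditional probability is 0.649, and the share without MetS is 35%.

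**5. What a register composite could recover, same assumptions.** The rule needs three of four components: glucose, blood pressure, obesity, and lipids met by either triglycerides or HDL. For r = 0:

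- P(lipid component) = 1 − (1 − 0.396)² = 0.635
- P(rule met) = q³ + 3q²(1 − q) × 0.635 = 0.062 + 0.180 = 0.242
- Share of MetS found = 0.242 / 0.31 = 78%

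At r = 0.4 the share is 86%. Inside this model everyone who meets the rule has MetS. That fails in practice where register components do not match Table 1.

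**The case against.** The substitution is deliberate and open. The design section gives the reason, the analysis section labels the conditions as proxies, and the limitations paragraph admits misclassification. Preferring a composite to declared proxies for a secondary outcome can be called a matter of taste, and an article may leave the derivation of a register phenotype to a fuller document. This stands against any suggestion of concealment, and it is why the composite is offered as a preference. It does not cure the power section, which makes a claim that the listed Cox outcomes do not deliver.

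Three stronger readings are tempting but not supported:

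- A reader might infer that no registry model serves the CST. The CST is described as a calculator for comorbidities generally, with MetS as a pilot case, so the CVD and type 2 diabetes models are in scope. The machine-learning outcome is unstated, so a MetS outcome there is not excluded.
- A reader might infer that any one condition will count as a MetS event and be carried into the CST. The protocol models named conditions separately and nowhere says their risks become MetS risks. The CST is to be tested in clinical-study patients not used for model development, which suggests that other clinical-study patients may be used for it.
- A reader might infer that registry risks will be too high. The illustration assumes perfect recording, and under-recording in registers could push recorded risk down.

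**Conclusion.** The point holds in a limited form. The power section for Study 1 claims models for MetS incidence and appears to count events by the three-of-five prevalence, while the only MetS-related Cox outcomes listed are three separate conditions. Disclosing the proxies does not link them to MetS.

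The minimum of 4,199 stands. The 12,000 events cannot be read as the expected count for any listed outcome. The 35% to 48% of single-criterion carriers without MetS, and the 78% to 86% of MetS found by the composite, rest wholly on the assumed model. They show that a single proxy is a different outcome and that a composite is worth considering; they do not predict register performance. This is worth correcting because MetS is the project's headline condition, but it concerns secondary outcomes and leaves the primary registry models untouched.

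**What to change.** **Minimum.** In the Study design and Power sections for Study 1, name the registry outcomes as CVD, type 2 diabetes and the individual MetS components, alongside the mortality outcomes. Remove the MetS-incidence claim. Replace the single event count with expected events for each outcome modelled. State the outcome of the machine-learning models. The cost is a wording change plus event estimates.

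**Preferred addition.** In the Data analyses section for Study 1, add a secondary outcome labelled as approximate register MetS: the date on which a third of four components (glucose/type 2 diabetes, hypertension, hyper/dyslipidaemia, obesity) is first recorded by diagnosis or dispensed treatment, in patients with fewer than three at baseline. Keep the single-condition models under their own names. The protocol already draws on diagnoses and prescriptions for these conditions, and Table 1 accepts treatment for four of its five criteria, so no new data source is needed.

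**Downsides to state with it.**

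- There will probably be fewer events than for single conditions.
- Untreated or unrecorded components are missed.
- The mapping to Table 1 is imperfect (recorded obesity is not waist circumference), so there will be some false positives.
- The outcome overlaps with the type 2 diabetes primary outcome.
- Patients with two components at baseline need only one more, so discrimination will partly reflect the baseline count. Performance should be reported by that count.
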